### 319 **Data collection methods**

320 All collected data will be obtained from the clinical records. Data collection forms are included in  
321 the electronic case report form (eCRF) that was specifically designed for the trial using a not  
322 validated web-based proprietary application that is compliant with the European regulations  
323 regarding electronic records and signatures. Subjects are identified by sex, birth date, and  
324 assigned trial number only, in accordance with personal data protection law. The study  
325 coordinator and trial statistician will review the generated results for logic, coherence, or  
326 problems. Outlier data will be investigated.

327 Once an infant is enrolled or randomized, the study site will make every reasonable effort to  
328 follow the infant for the entire study period.

329

### 330 **Ethics and Dissemination**

331

332 The study protocol has been carried out in accordance with the principles of the Declaration of  
333 Helsinki and approved by the following local ethical committees of the participating centers: the  
334 Pediatric Ethical Committee of Tuscany (Firenze), Ethical Committee of Milan-B Area (Milano),  
335 Ethical Committee of Bologna (Bologna), Ethical Committee of San Bortolo Hospital (Vicenza),  
336 Ethical Committee of Romagna (Rimini), Ethical Committee of Umbria (Perugia), Ethical  
337 Committee of Puglia (Bari), Ethical Committee of San Gerardo Hospital (Monza).

338 Possible protocol amendment during the study period will be submitted for approval to all the  
339 aforementioned ethical committees.

340 The study coordinator and trial statistician will have full access to the complete final dataset. Site  
341 investigators will have direct access to their own site's data sets, and will have access to other  
342 sites data by request, only after completion of the data analysis. The datasets during and/or  
343 analysed during the current study will be available from the corresponding author on reasonable  
344 request.

345 The results of the trial are expected to be published in a scientific journal and to be presented in  
346 medical seminars and conferences. The final reporting will follow the CONSORT Report  
347 guidelines (<http://www.consort-statement.org>).

348

## 349 **DISCUSSION**

350 PT strategies such as a short delay in cord clamping (30-60 sec) and cord UCM (with cord  
351 clamping within 20 sec of life) have been demonstrated to improve outcomes in preterm  
352 newborns (20,21).

353 It has been demonstrated that to perform initial neonatal resuscitation with PCI at mother bedside  
354 is feasible, safe and permits to obtain an effective lung ventilation before cord clamping (22,23).

355 Most preterm infants assisted at mother bedside with their cord intact start breathing  
356 spontaneously in the first minute of life (23). Newborns who start breathing or ventilating before  
357 cord clamping have better outcomes than newborns who start breathing or ventilating after cord  
358 clamping (24). In the ongoing UK Cord Trial preterm infants <32 weeks gestation randomized in  
359 the experimental arm receive cord clamping after at least 2 min of life and immediate neonatal  
360 care is given with intact cord, while the control arm receive an immediate cord clamping at birth.  
361 Our choice of performing cord clamping after 3 min of life in the study group is functional to leave  
362 the establishing of an effective ventilation of the lungs before clamping. But, it will be important to  
363 obtain a high adherence to the protocol in the experimental study group. The more physiological  
364 approach of stimulating spontaneous breathing or starting ventilation if necessary during the first  
365 180 sec of life before clamping the cord of very preterm newborns might result neuroprotective,  
366 reducing the intraventricular hemorrhage rate compared with cord milking. To date, there is  
367 evidence that cord UCM at birth has some benefits versus immediate cord clamping (7,8), so the  
368 priority is now to compare cord milking with delayed clamping (25), but the delay should be long  
369 enough to really consider the procedure a physiological-based cord clamping (26).

370 Thus, we hypothesized that clamping the cord after 3 min of life might be more beneficial than  
371 cord UCM in preterm infants <30 weeks gestation because during this period neonates can start  
372 to breathe/ventilate having the aforementioned hemodynamic advantage and a more  
373 physiological postnatal transition phase.

374

375 **LIST OF ABBREVIATIONS**

376 UCM: milking; PCI: placental circulation intact; PT: placental transfusion; eCRF: electronic case  

**LIST OF ABBREVIATIONS**

|      |                               |
|------|-------------------------------|
| ACA  | Anterior cerebral artery      |
| BPD  | Bronchopulmonary dysplasia    |
| CI   | Confidence interval           |
| ET   | Endotracheal                  |
| Hb   | Haemoglobin                   |
| Ht   | Haematocrit                   |
| iNO  | Inhaled nitric oxide          |
| IQR  | Interquartile range           |
| i.v. | Intravenous                   |
| IVH  | Intraventricular haemorrhage  |
| ITT  | Intention-to-treat            |
| min  | Minute                        |
| NEC  | Necrotizing enterocolitis     |
| PAP  | Pulmonary artery pressure     |
| PAS  | Systolic blood pressure       |
| PDA  | Patent ductus arteriosus      |
| PLV  | Periventricular leukomalacia  |
| PP   | Per-protocol                  |
| RDS  | Respiratory distress syndrome |
| ROP  | Retinopathy of prematurity    |
| SAE  | Serious adverse event         |
| SAP  | Statistical analysis plan     |
| SD   | Standard deviation            |
| SE   | Standard error                |

## 1 PREFACE

This Statistical Analysis Plan (SAP) is based on the version 4.0 of the trial protocol, dated December 22, 2016. The version 4.0 of the protocol amended the previous version 3.0, dated October 2, 2015, that was initially approved by the Ethical Committees and used in the first part of the trial. Previous versions were released during the development phase of the study protocol and were never adopted.

## 2 STUDY OVERVIEW

### 2.1 BACKGROUND

Placental transfusion, achieved by delaying the clamping of the umbilical cord at birth, results in better cardiorespiratory adaptation in preterm infants, an increase in mean arterial pressure and haematocrit levels in the first hours of life, improved tissue oxygenation at the cerebral and renal levels, a reduction in the number of red blood cell transfusions, a reduction in sepsis, reduced oxygen dependence, and, most importantly, a reduced incidence of cerebral haemorrhage (1, 2). Some have defined placental transfusion as the only 'drug' with proven therapeutic efficacy for the newborn in the delivery room (3).

If the umbilical cord is not immediately clamped at birth, within the first 3-5 minutes of life, there is a transfer of placental blood from the placenta to the newborn, estimated to be about 25-40ml/kg in term newborns delivered vaginally (4). In caesarean deliveries, this transfusion of blood to the newborn would occur within the first 40 seconds, after which there would be a reversal of flow favouring the placenta (5). Determinants for the occurrence of placental transfusion include uterine contractions, the patency of umbilical vessels, and the onset of effective respiration: the presence of uterine contractions (absent in caesarean delivery), vasoconstriction of the umbilical arteries but not the vein (mainly due to the increase in PaO2 at birth), and pulmonary vasodilation following effective respiration create the pressure gradient between placental and neonatal circulation that allows placental transfusion in the first minutes of life.

Not clamping the umbilical cord at birth, if postnatal adaptation progresses normally, allows placental blood to flow from the placenta to the newborn through the umbilical vein, then into the inferior vena cava, right atrium, right ventricle, pulmonary artery, and increasingly into the pulmonary circulation as pulmonary vascular resistance decreases (and in decreasing amounts from the right atrium to the left atrium through the foramen ovale, due to the progressive increase in pressure in the left heart sections). Thus, maintaining intact placental circulation ensures left ventricular filling (and thus left ventricular output) even if pulmonary vascular resistance does not decrease in the first minutes of life due to delayed postnatal adaptation (the oxygenated blood from the placenta will pass more into the systemic circulation through the foramen ovale and ductus arteriosus, as before birth). The gradual fall in pulmonary vascular resistance will ensure that left ventricular filling (and thus left ventricular output) is increasingly maintained by pulmonary flow and less by right-to-left shunt through the foramen ovale.

Placental transfusion thus maintains systemic cardiac output during the respiratory adaptation phase.

The onset of effective respiration/ventilation, with the consequent lung expansion, facilitates simultaneous pulmonary vasodilation, and the increased pulmonary flow would be at least partly ensured by placental transfusion (conversely, with immediate/early cord clamping, pulmonary flow could be ensured at the expense of systemic blood 'stolen' from other organs, such as the intestines). Increased pulmonary flow in a properly ventilated lung results in "capillary erection", which is the distention of perfused pulmonary capillaries that exerts an outward force against alveolar collapse during expiration, thus contributing to respiratory stabilization.

A recent study on preterm lambs (6) showed that clamping the cord at birth before the onset of respiration causes immediate reflex bradycardia (from average values of 160 bpm to 100 bpm) and persistent foetal circulation with a progressive reduction in right ventricular output; the subsequent improvement in pulmonary flow is then achieved by the initiation of artificial ventilation (at 2 minutes of life in the study design). Immediate cord clamping at birth also causes a sudden increase in pressure and flow in the carotid artery followed by a large reduction in flow with pressure adjustment (indicating a pressure-dependent flow in the carotid artery). In contrast, lambs ventilated for 3-4 minutes before cord clamping (until the demonstrated increase in pulmonary flow) showed, compared to those clamped immediately: 1) absence of bradycardia at the time of clamping, 2) doubled pulmonary flow, 3) stable carotid artery flow and pressure (no significant fluctuations), 4) higher pulmonary flow and right ventricular output still at 30 minutes.

Greater hemodynamic stability in the cerebral circulation in the first minutes of life could underlie the reduced incidence of cerebral haemorrhages in newborns benefiting from placental transfusion. Preterm infants undergoing delayed umbilical cord clamping have increased superior vena cava flow and a reduced incidence of severe cerebral haemorrhage (7).

The first minutes of life for preterm infants have been called "golden minutes", as during this brief period, the newborn undergoes the most complicated phase of physiological adaptation in their lifetime, and the type of care the newborn 'receives' can significantly impact their short- and long-term future, in terms of both mortality and morbidity (8). To ensure proper and timely care for the preterm infant in the delivery room, the neonatologist must follow international neonatal resuscitation guidelines (9), applying them as "gently" as possible, quickly ensuring respiratory support that provides effective ventilation. Therefore, it is necessary to clamp and cut the umbilical cord early in infants requiring some degree of assistance/resuscitation at birth, as is the case for nearly all extremely preterm infants, to position them on a neonatal resuscitation island. The initiation of neonatal resuscitation is the main reason for the lack of delayed cord clamping in preterm infants. To achieve placental transfusion without excessively delaying the start of neonatal care, the cord milking manoeuvre (rapid squeezing of about 20 cm of umbilical cord 4-5 times from the placenta to the newborn) can be performed. Cord milking results in a placental blood transfer in about 10-15 seconds equivalent to that obtained by not clamping the cord for about 30-60 seconds, with short-term positive

effects similar to those achieved with delayed clamping (10, 11). Cord milking allows for partial placental transfusion but does not benefit from the positive effect that the onset of effective newborn respiration would have on enhancing the efficacy of placental transfusion itself. Artificially achieved placental transfusion with cord milking could result in reduced positive effects compared to placental transfusion occurring physiologically in a newborn already effectively spontaneously breathing or, if necessary, adequately and promptly assisted. The effect of placental transfusion on postnatal adaptation is likely maximal in the newborn adapting well spontaneously or being adequately assisted in the first minutes of life to complete the transition phase while the cord is not clamped. Some foetal-placental pathological conditions such as chronic asphyxia may also cause a redistribution of foetal-placental blood volume with an increase in foetal blood volume that, especially if associated with reduced myocardial contractility, could be aggravated by rapid induced placental transfusion via cord milking.

Initiating care for the preterm infant “with intact placental circulation”, i.e. not clamping the umbilical cord, would likely achieve the maximum benefits demonstrated by placental transfusion without delaying the start of appropriate neonatal care. The number of studies demonstrating the benefits of placental transfusion in preterm infants, achieved by delaying clamping or performing cord milking, has increased considerably in recent years (10-16), and the lack of studies on infants assisted with intact placental circulation is mainly due to the difficulty of having a suitable setting to assist the newborn next to the mother's bed (17). At the time of the design of the PCIT1 trial, a randomized controlled trial (Cord Pilot Trial) was underway in England to verify the benefits of delayed cord clamping compared to immediate clamping, assisting infants, if necessary, near the mother's bed without clamping the cord. Initial data regarding the positive evaluation by professionals and parents of the bedside setting used in the trial to assist the newborn with intact placental circulation had been published (18, 19).

## 2.2 RATIONALE FOR PERFORMING THIS TRIAL

Based on these premises, we hypothesized that assisting preterm infants in the delivery room without clamping the umbilical cord at birth, thereby maintaining intact placental circulation, compared to assisting them after cord milking and early clamping, would result in better postnatal adaptation. This is demonstrated in the short term by a reduction in the need for mechanical ventilation within the first 24 hours, improved cerebral and intestinal hemodynamic parameters, and reduced use of plasma expanders or vasoactive drugs, and in the medium term by a reduction in severe complications such as severe cerebral haemorrhage, bronchopulmonary dysplasia, and mortality. The decision to compare assistance with intact placental circulation to assistance after cord milking, rather than to standard preterm infant care, which still does not widely include milking, is based on the positive scientific results published in favour of the latter procedure compared to standard care (i.e., immediate cord clamping without milking in infants with a gestational age of <30 weeks).

## 2.3 STUDY OBJECTIVES

### 2.3.1 Primary objective

To compare in the two groups of preterm infants in which assistance with intact placental circulation or assistance after cord milking has been given the proportion of subjects experiencing at least one of the following events at 36 weeks of post-conceptual age: grade 3 or 4 intraventricular haemorrhage (IVH), moderate or severe bronchopulmonary dysplasia (BPD) or death from any cause (composite outcome).

### 2.3.2 Secondary objectives

- To compare in the two groups of preterm infants in which assistance with intact placental circulation or assistance after cord milking has been given the proportion of subjects experiencing at 36 weeks of post-conceptual age each of the events included in the composite outcome.
- To assess the presence of interaction between type of assistance and gestational age, and between type of assistance and type of delivery, on the primary composite endpoint and on each of its components.
- To compare in the two groups of preterm infants in which assistance with intact placental circulation or assistance after cord milking has been given the results related to the identified secondary efficacy endpoints.
- To evaluate the safety of the two assistance strategies.

## 2.4 STUDY DESIGN

This is a prospective, two-stage, multicentric, open-label, randomized phase III study of assistance with intact placental circulation versus assistance after cord milking in preterm infants.

In the first part of the trial, 20 preterm infants have been enrolled in the study in order to evaluate the feasibility of the experimental procedures. In the second part of the trial, the enrolment of the overall planned study population was completed. The first 20 accrued patients were included in the final statistical analysis.

## 2.5 STUDY POPULATION

### 2.5.1 Inclusion criteria

Infants who mainly met the following criteria were eligible for participation into the trial:

- Newborn with a gestational age between 23+0 and 29+6 weeks
- Informed consent form signed by the parents

### 2.5.2 Exclusion criteria

Patients were excluded from participation into the trial if they met one or more of the following main criteria:

- Major congenital malformations
- Foetal hydrops
- Pregnancy complicated by placental abruption
- Pregnancy complicated by Rh isoimmunization
- Twin pregnancy
- Short umbilical cord\*

\*This criterion was removed in the amended version 4.0 of the protocol, dated December 22, 2016, due to the recurring inability, discovered in the first part of the trial, to identify cases with a short umbilical cord before randomization.

## 2.6 INTERVENTIONAL GROUPS

Preterm infants were randomly allocated to one of the two interventional arms reported in Table 1.

**Table 1:** The two interventional arms of the study.

| Arm      | Intervention                                                                                                                                   |
|----------|------------------------------------------------------------------------------------------------------------------------------------------------|
| A | Control: assistance on the neonatal resuscitation table, after performing cord milking followed by umbilical cord clamping              |
| B | Experimental: assistance with intact placental circulation, keeping the newborn near the mother's bed at the same level as the placenta |

## 2.7 SAMPLE SIZE

Assuming a proportion of events (grade 3 or 4 IVH, moderate or severe BPD or death from any cause) equal to 47% in the control arm and equal or less than 28% in the experimental arm, corresponding to a relative reduction of the unfavourable events equal to 40%, it was calculated that a sample size of 200 preterm infants (100 per group) would have guaranteed a study power equal to 80%, with a two-sided alpha error equal to 5%, for a standard chi-square test for heterogeneity.

## 2.8 TREATMENT ALLOCATION

Assignment of each preterm infant to one of the two interventional groups has been performed using a minimization algorithm, with an allocation ratio equal to 1:1.

Minimization is a dynamic randomization algorithm designed to minimize imbalance between treatments taking stratification factors into account. Based on characteristics of

the current patient and treatment assignments and characteristics of enrolled patients an imbalance score is computed. In the present study, the assignment was performed using a randomization list with an allocation ratio equal to 1:1 in absence of imbalance. A random component in intervention selection was also used in case of imbalance. Indeed, in this situation, a randomization list with an allocation ratio equal to 1:5 in favour of the intervention with the highest imbalance score was used.

The gestational age (23+0 to 26+6 versus 27+0 to 29+6) has been used as a stratification factor.

Treatment allocation process has been carried out at all participating centres by a restricted access web-based system (<https://www.eclintrials.org/ect>), administered by the Clinical Epidemiology Unit of the IRCCS Ospedale Policlinico San Martino, Genoa, Italy, active 24-hour, and 365 days a year.

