## 161 **TREATMENT OF SUBJECTS**

### 162 **Randomization**

163 Infants at each unit are randomly assigned in blocks to a treatment group (PCI or UCM) in a 1:1  
164 ratio. The allocation sequences consist of computer generated random numbers. Since the  
165 frequency of the composite primary outcome is inversely related to gestational age, the inclusion  
166 of patients is balanced in each treatment group according to the following gestational ages: 23+0  
167 to 26+6 weeks or 27+0 to 29+6 weeks.

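### SAP 2.8 describes a minimisation rule that is inverted under the usual meaning of an imbalance score, and the scheme differs from the protocol's blocks at each unit

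*Combined protocol and SAP*

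**What the plan says.** SAP 2.8 says that assignment was "performed using a minimization algorithm, with an allocation ratio equal to 1:1". It gives the purpose: "Minimization is a dynamic randomization algorithm designed to minimize imbalance between treatments taking stratification factors into account". For each new infant "an imbalance score is computed", but the section gives neither a formula nor a direction for it. Allocation used "a randomization list with an allocation ratio equal to 1:1 in absence of imbalance"; otherwise, "a randomization list with an allocation ratio equal to 1:5 in favour of the intervention with the highest imbalance score was used". One factor is listed: "The gestational age (23+0 to 26+6 versus 27+0 to 29+6) has been used as a stratification factor". Centre and blocks are not mentioned.

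The protocol's Randomization section says: "Infants at each unit are randomly assigned in blocks to a treatment group (PCI or UCM) in a 1:1" ratio. It adds: "The allocation sequences consist of computer generated random numbers". It balances on the same two gestational-age bands.

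The SAP Preface says that the SAP rests on protocol version 4.0. No section of either document mentions a change of allocation method. SAP 5.2.2 fits the primary logistic model with arm as the only covariate.

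**The concern.** There are two separate problems.

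First, the direction of the biased coin. Minimisation should favour the arm whose choice leaves the smaller imbalance. Under the usual definition of the score, that is the arm with the lowest value. As written, the coin goes to the highest, against the aim stated in the same section.

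Second, the scheme itself. Blocks within each unit and minimisation on gestational age are different methods, and both cannot describe how the infants were allocated. The difference bears on the analysis, because the model should reflect the factors used in allocation. It also bears on the trial report, which the protocol says will follow CONSORT.

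The protocol states that the composite outcome is inversely related to gestational age. A rule that pushed the strata apart could therefore confound arm with a strong prognostic factor.

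**Working it through.** **Inputs.** From the documents: two gestational-age strata; 1:1 when balanced; 1:5 otherwise, that is 5/6 against 1/6 (SAP 2.8); event proportions 47% and 28%, two-sided alpha 5%, 100 per group for 80% power (SAP 2.7); 106 per group with 5% dropout (protocol, Sample Size Calculation); eight units (protocol, Study population). Assumed: the share of infants in the smaller gestational-age stratum, which the documents do not give, taken as 30%, 40% or 50%.

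**The plan's own figure.** With pooled variance and mean proportion 0.375:

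n = [1.960·√(2·0.375·0.625) + 0.842·√(0.47·0.53 + 0.28·0.72)]² / 0.19² = (1.342 + 0.565)² / 0.0361 ≈ 100.7, so 101 per arm against 100 stated.

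Power at 100 per arm is 79.7%. Dropout: 100/0.95 = 105.3, so 106. The sample-size figures reproduce within rounding and do not depend on the minimisation sentence.

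**Literal rule, usual score.** Once a stratum is off balance, each infant moves it further by 5/6 − 1/6 = 2/3 on average. A stratum of 106 drifts by about 106 × 2/3 = 70.7. The two strata drift independently, so they go the same way about half the time and opposite ways about half the time:

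| Split of 212 | Expected drift by stratum | Same way | Opposite ways | Simulated mean overall difference |
|---|---|---|---|---|
| 50:50 | 70.7 and 70.7 | 141 | near 0 | 76–78 |
| 40:60 | 56.5 and 84.8 | 141 | 28 | 85–86 |
| 30:70 | 42.4 and 98.9 | 141 | 57 | 99–100 |

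The last column gives two independent simulations (10,000 and 20,000 trials). The mean within-stratum difference was about 71 at N = 212 for all three splits.

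**What arm totals would show.** With equal strata and N = 212, the overall difference exceeded 20 in 58% of simulated trials. In the other 42% it was 20 or less, although the strata differed by about 71 on average. Even totals therefore do not rule out a literal inversion.

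**Comparison at N = 212.**

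| Rule | Mean overall difference | Mean within-stratum difference | Mean power |
|---|---|---|---|
| 5/6 to the under-represented arm | about 1 (95th percentile 2) | about 0.75 | 82% |
| Simple 1:1 | about 11 to 12 | about 8 | 82% |
| 5/6 to the over-represented arm | 76–100 | about 71 | 67–69% |

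Under the literal rule the larger arm holds 68% to 74% of infants on average. At N = 200 its mean power is 65% to 67%, against 79.7% for the intended rule. These power figures reflect unequal arm sizes only, not bias from confounded gestational age.

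**Centre.** Suppose minimisation worked as intended, on gestational age alone, with 212 infants, eight equal centres and equal strata. The mean absolute arm difference per centre is then 3.8, and the median worst-centre difference is 8. Blocks within unit would limit this.

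**The case against.** The strongest reply is that the score is undefined, not shown to be wrong. If it measures how under-represented an arm is, the highest score belongs to the arm that needs infants, and the sentence describes a proper biased coin. The stated aim and the overall 1:1 ratio both point to that intention. This stands as far as it goes: the wording cannot show what the system did. It does not rescue the text, because a reader who applies the usual definition gets the opposite rule.

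Three stronger readings are tempting, and the documents do not support them.

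- *The trial was in fact badly unbalanced.* No section reports arm counts or suggests this.
- *The overall difference would be about 141 (212 × 2/3).* That treats the trial as one stratum, or assumes that both strata drift the same way. SAP 2.8 has two strata, and the mean is about 76 to 100.
- *Nothing balanced the arms within units.* SAP 2.8 lists gestational age as a factor and does not say that it was the only one. Centre is unlisted, but its absence from the system is not shown.

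It is also fair to say that the planned displays would reveal much. Table 1.2 gives arm totals, Table 1.4 arm by centre, and Table 2.3 arm by gestational-age band. The interaction model in 5.2.2 gives odds ratios within gestational-age bands. These help, but the headline odds ratio remains unadjusted, and no table settles which scheme was used.

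Finally, the documents give no variation in outcome between centres, so a centre model irrespective of the allocation factors is a preference.

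**Conclusion.** The point holds in two parts. The conflict between the protocol's blocks at each unit and the SAP's minimisation is plain, and nothing reconciles it. The biased-coin sentence is inverted under the usual definition of the score and otherwise undefined, so it cannot stand as written.

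The consequence is conditional. If the system ran the literal rule, the differences would be those worked out above, with gestational age possibly confounded with arm behind even totals. They rest on the usual definition of the score and the assumed gestational-age splits. If the wording is merely inverted, or the score is a deficit, balance would be close, with a mean overall difference of about 1. The documents do not say which case applies; the allocation log will.

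**What to change.** 1. Have the unit that runs the web system check its configuration and log, without outcome data and without passing arm counts to the blinded SAP author. Of the assignments made when the stratum was unbalanced, about 5/6 (83%) should have gone to the under-represented arm. Review arm counts by gestational-age band and by centre (Tables 2.3 and 1.4), not totals alone.
2. If the log confirms the intended rule, change *highest* to *lowest* in SAP 2.8, or define the score and state which arm receives probability 5/6. If the log shows that the literal rule ran, report that instead of rewording it.
3. Make the protocol and the SAP state the one scheme actually used, including whether unit was a factor.
4. Adjust the primary logistic model, or a stated sensitivity model, for the factors used in allocation: gestational-age band, and unit if it was used. If unit was not a factor, a centre-adjusted sensitivity model is optional.

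The cost is one log check, corrected wording in two documents and one adjusted model. No new data are needed. Settle it before database lock.
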